### Intervention and randomisation

999 calls in the main trial site during the six observation weeks (up to 42 days; 84 shifts) will be randomised 1:1 to working shift intervention or standard care. Control shifts will follow standard care ambulance dispatch protocol with a 999 caller using a telephone (voice only) and the call taker using NHS Pathways ambulance dispatch tool.

In the intervention arm, a live streaming technology called GoodSAM Instant-on-Scene^23^ will be tested. The technology allows a 999 caller to stream live video footage from the scene of an incident to the EOC. 999 calls allocated to intervention will initially follow the standard NHS Pathways dispatch protocol until ambulance dispatch prioritisation has been determined. EMS will be dispatched as normal, without delay. The call handler in the EOC will then transfer the caller to the HEMS dispatcher or critical care paramedic (CCP) and live streaming will be activated. EMS resource allocation may be adjusted following this.

If at any point the dispatcher feels they do not want to view the scene (eg, due to psychological impact of viewing the scene) or it is not safe to continue, the 999 caller will be thanked for their help and the call will be ended. The dispatchers will be provided with training and guides outlining the trial processes to ensure adherence to intervention and study protocols.

### Outcomes

#### Primary outcomes

The primary outcome is the decision regarding the feasibility of undertaking a definitive RCT based primarily on meeting the specified progression criteria (see table 3).

**Table 3 T3:** Progression criteria from feasibility RCT to future RCT

GREEN; proceed to definitive study—GO	AMBER; consider protocol amendments to improve criteria	RED; do not proceed to main trial—STOP
≥70% of callers with smartphones agreeing and able to activate live streaming	≥50% of callers with smartphones agreeing and able to activate live streaming	<50% of callers with smartphones agreeing and able to activate live streaming
≥50% of requests to activate live streaming resulting in footage being viewed	≥30% but <50% of requests to activate live streaming resulting in footage being viewed	<30% of requests to activate live streaming resulting in footage being viewed
Air Ambulance (HEMS) stand-down rate reducing by ≥10% and/or change in dispatch decision as a result of live streamed footage confirmed as being appropriate in ≥10% cases	Air Ambulance stand-down rate reducing by ≥5% and/or change in dispatch decision as a result of live streamed footage confirmed as being appropriate in ≥5% cases	No change in Air Ambulance stand-down rate and/or change in dispatch decision as a result of live streamed footage
Rates of psychological harm (based on the survey measures) not significantly greater in 999 callers using live streaming compared with those not; and no significant difference in change to psychological harm over time in staff (CCPs, HEMS dispatchers, research paramedics) compared with change in staff in a comparison EOC not using live streaming/streamed from scene footage	–	Evidence of significantly greater harm in either 999 callers or EOC staff using live streaming compared with EOC not using live streaming.

CCP, critical care paramedic; EOC, emergency operations centre; HEMS, helicopter emergency medical services; RCT, randomised controlled trial.

In addition to the quantitative progression criteria described in table 3, the research team will consider qualitative data collected as part of this study (eg, interviews, observations and free text questions in surveys) when reviewing progression to a definitive RCT.

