**Trial registration number:**

ISRCTN11449333.

Strengths and limitations of this studyThe mixed methods approach to evaluation of feasibility and acceptability uses a combination of routinely collected data, observational data, interviews and survey methods.A comprehensive process evaluation will be undertaken to understand acceptability and impact of using live streaming from the perspective of 999 callers and emergency operations staff.The design (testing for a week each month over 6 months) builds consideration of seasonal variation in trauma into the design, while enabling time to adapt and improve the protocol as the SEE-IT Trial progresses.Recruitment of 999 callers may prove challenging due to the nature of their involvement in incidents; and investigating any impact of wider diversity factors is dependent on the characteristics of callers during the trial periods and we may not have sufficient data for this. The Ambulance Trust where live streaming will be tested uses NHS Pathways (as used in half of Ambulance Trusts in the UK); the SEE-IT Trial will give us insight into how live streaming would work with this dispatch system but may not extrapolate fully to areas that use other systems for triage/decision support.

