### Objectives and research questions

Main research question: is it feasible to conduct a future randomised controlled trial (RCT) to assess the clinical and cost effectiveness of using GoodSAM live video streaming to improve targeting of emergency medical resources? The overall aim of this research is to assess the feasibility of implementing and evaluating GoodSAM live streaming in a definitive RCT.

The objectives are:

To obtain data required to inform the design of a subsequent RCT (eg, event rate, screening rate, effect size/precision for outcomes health economic data).To test trial processes including randomisation and data collection methods.To conduct a nested process evaluation to test the acceptability and feasibility of using GoodSAM live streaming from provider and public perspectives (eg, training, video feasibility, video acceptability, psychological harm to 999 callers and/or dispatch staff).

Further research questions relating to these objectives can be found in the study protocol published on the National Institute for Health and Care Research (NIHR) study webpage.^22^

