#### Secondary outcomes

Speed of appropriate EMS dispatch: speed will be measured using time-stamped data from start of 999 calls to appropriate deployment with judgement of ‘appropriateness’ to be based on algorithms developed through expert consensus (see below) and using medical records data up to 3 months post-incident where consent is provided; stand-down rate (de-escalation); missed jobs (eg, not prioritised for HEMS/CCP despatch, either due to lack of resource or inappropriate prioritisation); requests for further ambulance resources from scene. Psychological harm will be assessed using two validated scales^24 25^ pre-trial and post-trial in 999 callers from both arms and staff viewing the footage (including staff in comparison EOC).

The appropriateness of dispatch will be determined based on algorithms developed through expert consensus before the trial starts. Appropriateness is defined as the need for intervention and/or transport by the response vehicle/staff dispatched to scene (eg, for HEMS dispatch that a critical care intervention and/or transportation by helicopter was required^9^). A binary outcome decision tree will be developed with the reasons for appropriate/inappropriate dispatch categorised and agreed (inappropriate dispatch will be further categorised as being ‘over’ or ‘under’ resourced).

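### Table 3 has no criterion for whether the consent- and survey-dependent outcomes can be collected, so all four rows can be GREEN on sparse appropriateness ratings and few caller surveys

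*Protocol article*

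**What the plan says.** Under Primary outcomes: "The primary outcome is the decision regarding the feasibility of undertaking a definitive RCT based primarily on meeting the specified progression criteria". Table 3 then gives four rows. Their GREEN conditions are:

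- Row 1: "≥70% of callers with smartphones agreeing and able to activate live streaming".
- Row 2: "≥50% of requests to activate live streaming resulting in footage being viewed".
- Row 3: "Air Ambulance (HEMS) stand-down rate reducing by ≥10% and/or change in dispatch decision as a result of live streamed footage confirmed as being appropriate", the latter in at least 10% of cases.
- Row 4: "Rates of psychological harm (based on the survey measures) not significantly greater in 999 callers using live streaming compared with those not", together with a staff comparison against the EOC that does not stream. The AMBER cell of this row is empty.

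The only further evidence named for the decision is qualitative.

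The second objective is "To test trial processes including randomisation and data collection methods". Under Secondary outcomes, appropriateness is judged with expert-consensus algorithms and "using medical records data up to 3 months post-incident where consent is provided"; speed of dispatch is timed to the appropriate deployment, so it depends on the same judgement. Caller harm comes from an online survey 6–8 weeks after the incident, and the strengths and limitations list warns: "Recruitment of 999 callers may prove challenging due to the nature of their involvement in incidents". The Quantitative analysis section promises estimates with confidence intervals for eligible calls per day and for timing and appropriateness of dispatch, and a summary of missing data. It links none of these to the progression decision.

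**The concern.** Rows 1 and 2 concern delivery of the intervention, row 3 is an effect signal and row 4 a safety signal. How completely the trial obtains the outcomes that rest on consented records or on survey return affects no colour. If few incidents can be rated and few callers respond, that is a finding about the feasibility of the definitive trial, but Table 3 does not register it as one. In row 4 it works the wrong way: fewer responses make the GREEN condition easier to meet. The trial could then report GO on every row without having shown that these three outcomes can be collected.

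**Working it through.** **Inputs from the document.** About 250 incidents, 125 of them allocated to intervention; up to 42 observation days; about 250 callers at the main site; event-rate precision of ±0.75 per day; SE below 5% for speed to appropriate response (Sample size; Intervention and randomisation).

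**1. The plan's own figures.**

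- Event rate: 250/42 = 5.95 per day. The Poisson 95% half-width is 1.96 × √250 / 42 = 0.74 per day, which agrees with ±0.75.
- SE below 5%: no formula is given. Read as a proportion at p = 0.5 (an assumption), √(0.25/125) = 4.5% per arm and √(0.25/250) = 3.2% overall. Both meet the claim if every incident is rated.

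**2. What the SE claim implies for completeness.** On the same reading, an SE of 5% needs 0.25/0.05² = 100 rated incidents. Per arm that is 100/125 = 80%; with both arms pooled it is 100/250 = 40%. Per arm:

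| Share rated | Incidents rated | SE |
|---|---|---|
| 100% | 125 | 4.5% |
| 80% | 100 | 5.0% |
| 60% | 75 | 5.8% |
| 40% | 50 | 7.1% |
| 20% | 25 | 10.0% |

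No row of Table 3 changes colour because of the share rated as such.

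**3. Row 3.** The two limbs are joined by and/or, so a stand-down reduction of at least 10% gives GREEN with no incident rated for appropriateness.

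**4. Row 4, caller part.** GREEN requires only that harm is not significantly greater, and no minimum response is set. Assumptions, none from the document: 125 callers invited per arm, equal response in both arms, two-sided 5% test, shift clustering ignored, and true harm rates as shown. The entries are the probability of no significant excess harm, 1 − power. The first figure is from the normal approximation and the second from Fisher's exact test.

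| Response | Responders per arm | 20% vs 40% | 20% vs 30% |
|---|---|---|---|
| 100% | 125 | 6% to 8% | 55% to 61% |
| 60% | 75 | 23% to 29% | 71% to 77% |
| 40% | 50 | 41% to 48% | 79% to 85% |
| 20% | 25 | 67% to 77% | 88% to 93% |
| 10% | 12 | 82% to 91% | 92% to 97% |

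These figures are for the caller comparison alone. Row 4 as a whole also needs the staff comparison to be non-significant, so the chance that the full row is GREEN cannot be higher than shown.

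**5. Rows 1 and 2.** Both are percentages of callers or requests and do not involve hospital records or the survey.

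**The case against.** The strongest reply is that the table is not mechanical. The decision rests primarily, not solely, on Table 3. Qualitative evidence is weighed as well, and the EOC observations include fidelity to the protocol. Missing outcome data will be summarised, so the team will see poor completeness. This stands in part: the information will be available. But the only addition the text names is qualitative, and no level of completeness is tied to the decision.

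Second, a reader might infer that nothing in Table 3 bears on running an RCT, or that the definitive trial could be left unable to measure its outcomes in general. The document supports neither. Rows 1 and 2 show whether the intervention arm can be delivered. Stand-down rate, missed jobs and requests for further resources are not stated to need consent or a survey; research paramedics record dispatch decisions live and retrieve time-stamped data afterwards.

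Third, a reader might infer that the plan itself doubts consent. It names only caller recruitment as uncertain. For patients it sets out consultee, parent or guardian, telephone, email and postal routes, and approval to use the records of those who die before consent can be sought. Low completeness is a possibility the criteria should cover, not one the plan predicts.

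Fourth, row 3 may partly protect itself. If its 10% is taken over all viewed streams, unrated incidents make the appropriateness limb harder to pass. That is a fair reading, but the stand-down limb still gives GREEN on its own.

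Fifth, it is tempting to ask for a progression row on eligible incidents per day. The definitive trial is to be multicentre, so a low rate at one site affects the number of sites and the duration; it does not show that the trial is infeasible.

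**Conclusion.** The point holds in limited form. Table 3 sets no level for completeness of appropriateness rating or for caller-survey response, although testing data collection is an objective and the table is the main basis of the primary outcome. All four rows can be GREEN when appropriateness of dispatch, speed of appropriate dispatch and caller harm are poorly captured. The data are to be collected; what is missing is their link to the decision.

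The size can only be illustrated. With assumed harm of 20% versus 40%, the chance that the caller comparison raises no alarm goes from about 8% at full response to about 77% at 20% response (Fisher). With 20% versus 30% it is already 61% at full response and reaches 93%. The 80% per-arm completeness benchmark depends on reading the SE claim as a per-arm proportion at p = 0.5; pooled over arms it would be 40%. The absence of the criteria does not depend on any of these assumptions.

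**What to change.** (a) Add a row to Table 3: share of eligible incidents with appropriateness rated, taking the lower arm. As an example, GREEN at 70% or more, AMBER from 50% to below 70%, RED below 50%. These cut-offs are proposals for the steering committee to confirm before outcome data are reviewed. For reference, 70% of 125 is 87.5 incidents, with SE √(0.25/87.5) = 5.3%, slightly wider than the stated 5% on the per-arm reading; the committee may prefer a GREEN limit nearer 80%.

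(b) Fill the empty AMBER cell of row 4 with a condition such as: too few responses to judge harm. It applies when caller-survey response in either arm is below a level the committee fixes, so that GREEN cannot rest on non-significance in a small sample.

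(c) Add no row for incidents per day. Report that rate with its confidence interval as already planned, and use it to set the number of sites and the duration of the multicentre trial.

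The cost is a table change with committee approval and no new data. The downside is one more row, and one more way for row 4 to miss GREEN. The trial weeks ran from June to November 2022 and the version described is dated 7 November 2022, so pooled completeness may already be partly known. The committee should record what it had seen when it fixed the cut-offs.

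### Row 3 of the progression table can be GREEN while footage-led dispatch changes rated inappropriate outnumber those rated appropriate

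*Protocol article*

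**What the plan says.** **The decision rule.** Under Primary outcomes, the primary outcome is the decision on whether a definitive RCT is feasible, resting primarily, though not solely, on Table 3. Qualitative data are also considered.

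**Row 3 of Table 3** has two limbs joined by and/or: "Air Ambulance (HEMS) stand-down rate reducing by ≥10% and/or change in dispatch decision".
- GREEN, changed-decision limb: "change in dispatch decision as a result of live streamed footage confirmed as being appropriate in ≥10% cases".
- AMBER, same limb: "change in dispatch decision as a result of live streamed footage confirmed as being appropriate in ≥5% cases".
- RED: "No change in Air Ambulance stand-down rate and/or change in dispatch decision as a result of live streamed footage".

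**Row 4**, the only harm row, concerns psychological harm. Its GREEN cell begins "Rates of psychological harm (based on the survey measures) not significantly greater in 999 callers using live streaming compared with those not" and its RED cell begins "Evidence of significantly greater harm in either 999 callers or EOC staff using live streaming".

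**Elsewhere in the article.** Intervention and randomisation says that, once streaming has been activated, "EMS resource allocation may be adjusted following this". Secondary outcomes plans a binary appropriateness rating and adds that "inappropriate dispatch will be further categorised as being ‘over’ or ‘under’ resourced". Missed jobs and requests for more resources from scene are also secondary outcomes. None of these has a progression threshold.

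**The concern.** The plan defines a two-sided rating, appropriate or inappropriate, but its decision rule uses only the favourable side. Footage can lead a dispatcher to change the allocation in a way later rated inappropriate, including under-resourced. The authors foresee this, because they build the over/under split into the rating. Yet Table 3 does not count, cap or subtract such changes.

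A definitive trial could thus be supported by a GREEN on the dispatch row when the dispatch evidence, taken as a whole, points the other way. The table would also have no clear place for an unfavourable result. This is not detail that a protocol would leave to the SAP, because Table 3 fixes the criterion here.

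**Working it through.** **Inputs from the protocol article.** About 250 incidents, 125 of them intervention (Sample size); up to 42 days (Intervention and randomisation); GREEN at 10% and AMBER at 5% in row 3; GREEN in row 2 when at least 50% of requests lead to viewed footage.

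**Planning basis.** The stated event-rate precision is ±0.75 per day. Rate = 250/42 = 5.95 per day; 95% half-width = 1.96 × √250 / 42 = 0.74. This agrees, so 250 incidents (125 intervention) is a sound basis for the counts below.

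**Minimum count for GREEN.** The article does not define *cases*, so three readings are taken. The minimum is 10% of N, rounded up.

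| Reading of *cases* | N | Appropriate changes needed | Inappropriate changes compatible with GREEN |
|---|---|---|---|
| All intervention incidents | 125 | 13 (10.4%) | 0 to 112 (125 − 13); 14 or more outnumber the appropriate |
| Viewed calls, assuming half of 125 (62.5, taken as 63) | 63 | 7 (11.1%) | 0 to 56 (63 − 7); 8 or more outnumber the appropriate |
| Changed decisions only | number changed | 10% of changes | up to 90% of changes |

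Example on the second reading: 7 appropriate and 12 inappropriate changes give GREEN, with a balance of (7 − 12)/63 = −7.9% of viewed calls. The figure of 12 is an assumption.

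On the third reading inappropriate changes do enter the denominator and lower the percentage, but 2 appropriate and 18 inappropriate changes out of 20 still give 10% and GREEN.

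**How often this could happen under assumed true rates.** The article gives no such rates. These come from a multinomial simulation of 200,000 draws, counting trials that are GREEN on this limb.

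| Assumed appropriate / inappropriate | N | GREEN | GREEN with more inappropriate than appropriate |
|---|---|---|---|
| 12% / 20% | 125 | 75% | 68% |
| 12% / 20% | 63 | 64% | 49% |
| 15% / 20% | 125 | 95% | 75% |
| 12% / 12% | 125 | 75% | 24% |

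**A wholly unfavourable result.** Suppose no changes are confirmed appropriate and 20% of cases have changes rated inappropriate. On this limb that is below the 5% needed for AMBER, and it is not an absence of change, so it fits no cell. Whether the row as a whole is then RED depends on the stand-down limb and on how the and/or is read.

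**Does another rule close the gap?** The stand-down limb can deliver GREEN alone and puts no limit on inappropriate changes. Rows 1 and 2 concern uptake and viewing. Row 4 covers callers and staff. The Harms section addresses serious breaches and protocol deviations, which need not include an inappropriate dispatch made within protocol. No stated rule supplies the missing limit.

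**The case against.** The strongest reply is that this is a feasibility study. GREEN means a definitive RCT may go ahead, and that RCT would test clinical effectiveness. The article says the study is not powered for efficacy and limits interpretation to direction and magnitude. Leaving the balance of good and bad dispatch changes outside a feasibility gate is arguable. This stands as a limit on the consequence. But the sponsor has already placed dispatch benefit inside the gate through row 3, and a criterion that admits the benefit should admit its opposite.

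A reader might infer more than the documents support, and four points of the reply hold:
- *That live streaming makes dispatch worse for more patients than it helps.* The rating asks whether the resource sent was needed, not whether the change improved on the decision before video. A changed dispatch rated inappropriate may be no worse than the one it replaced.
- *That inappropriate changes cannot reach the decision.* Table 3 is the primary basis, not the only one. Appropriateness and the secondary outcomes will be summarised by arm to inform the next trial. What is missing is a limit, not the information.
- *That inappropriate changes count for nothing on any reading.* If *cases* means changed decisions, they dilute the percentage, though weakly.
- *That every changed decision will be rated.* The rating draws on medical records where consent is given, so some changes may lack the data.

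One might also ask for a net percentage, appropriate minus inappropriate. That would let an over-resourced and an under-resourced error offset an appropriate change equally, so it could itself hide under-resourcing.

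**Conclusion.** The point holds as a gap in the decision rule and should be fixed. As worded, row 3 can be GREEN with inappropriate footage-led changes outnumbering appropriate ones under all three readings of *cases*: 13 appropriate changes of 125 incidents, or 7 of about 63 viewed calls, are enough, and on the narrowest reading up to 90% of changes may be inappropriate. A result with only inappropriate changes has no cell on this limb.

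The counts rest on the planned 125 intervention incidents and, for 63, on an assumed 50% viewing rate. The simulated percentages rest on assumed rates and show possibility, not expectation. The conclusion concerns row 3 only: overall progression also needs the other rows and allows qualitative judgement, and it leads to another trial. The documents do not support reading this as evidence of patient harm or as a flaw that invalidates the study.

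**What to change.** In Table 3, and in the SAP that the steering committee approves before analysis:

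1. State the denominator of *cases*. All intervention incidents or all viewed calls would keep the thresholds meaningful. With changed decisions as denominator, the condition in item 2 would largely override the 10% threshold.
2. Keep the 10% and 5% thresholds, and add that row 3 cannot be GREEN, and is RED on the changed-decision limb, when footage-led changes rated inappropriate equal or exceed those rated appropriate.
3. Extend RED from no change to no change or worse.
4. Show changes rated under-resourced, and changes that could not be rated, as separate lines beside row 3 when progression is decided.

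**Effect.** At N = 125 with assumed rates of 12% appropriate and 20% inappropriate, GREEN on this limb falls from 75% to at most about 6% (74.7% − 68.3% = 6.4%; ties reduce it further). With equal rates of 12% it falls to at most about 50% (74.7% − 24.3% = 50.4%). Where inappropriate changes are rare, little is lost.

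**Cost.** Wording only; the rating and its over/under split are already planned. The criterion becomes somewhat harder to meet, and changes without enough data to rate stay outside both counts, which is why they need their own line. The change is late: the article describes the version of 7 November 2022 and recruitment began on 18 June 2022. It should be dated and recorded as made before the appropriateness ratings are tabulated.

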### Statistical methods and data analysis

#### Quantitative analysis

A full statistical analysis plan (SAP) will be reviewed by key members of the research team and approved by the steering committee before analysis is undertaken.

As this is a feasibility study, statistical analysis will focus on providing estimates and confidence intervals of key rates such as the number of eligible calls per day, uptake of video intervention and timing and appropriateness of dispatch to inform a subsequent RCT. Outcome measure will be summarised by arm and estimates reported with confidence intervals to inform future sample size calculations.

The SAP will outline any expected exploratory analysis of outcomes that may be useful to inform a subsequent RCT including any signal of potential efficacy, but it is noted that the study is not powered for this and so any interpretation would be limited to the direction and magnitude of any effect. Missing data (including outcome data) will be summarised, but all observed data will be included in any analysis according to the randomised allocation following the intention-to-treat principle.

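### The harm row of Table 3 counts an inconclusive comparison as GREEN: it uses non-significance with no margin and leaves the AMBER cell empty

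*Protocol article*

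**What the plan says.** In the protocol article, under Primary outcomes, the primary outcome is the decision on whether a definitive trial is feasible, based primarily on Table 3. The fourth row of that table is the only one on harm.

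- **GREEN, callers:** "Rates of psychological harm (based on the survey measures) not significantly greater in 999 callers using live streaming compared with those not".
- **GREEN, staff (also required):** "no significant difference in change to psychological harm over time in staff", against a comparison emergency operations centre.
- **RED:** "Evidence of significantly greater harm in either 999 callers or EOC staff using live streaming".
- **AMBER:** a dash. The column is headed "AMBER; consider protocol amendments to improve criteria", and the other three rows each have a threshold in it.

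The row gives no margin, confidence limit, significance level or minimum number of respondents. The Sample size section gives head-counts: 250 main-site callers, and up to 86 staff at each of the two centres compared. Its only precision statements concern the event rate and speed to appropriate response.

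The Quantitative analysis section says that "statistical analysis will focus on providing estimates and confidence intervals of key rates". Of exploratory outcome analyses it says that "the study is not powered for this and so any interpretation would be limited to the direction and magnitude of any effect". The strengths and limitations box adds that "Recruitment of 999 callers may prove challenging due to the nature of their involvement in incidents".

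**The concern.** A test that fails to reach significance may mean that harm is absent, or that too few people answered for harm to show. The row does not separate the two. With only GREEN and RED available, a result too imprecise to say anything is recorded in the same cell as a reassuring one.

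The incentive also runs the wrong way. If there is a true excess of harm, each lost survey response makes the criterion easier to pass. A significance test as gatekeeper also sits badly with an analysis section built on estimates and intervals. At stake is the harm part of the go/stop decision, for an exposure whose psychological impact the Introduction says has not been investigated in trauma.

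**Working it through.** **1. The plan's own figures.** With 250 incidents in 42 days the rate is 250/42 = 5.95 per day. The Poisson 95% half-width is 1.96 × √250 / 42 = 0.74, against a stated ±0.75. The worst-case SE of a proportion is √(0.25/125) = 4.5% at 125 and √(0.25/250) = 3.2% at 250, against a stated limit of 5%. Both reproduce. There is no stated figure for harm to reproduce.

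**2. Inputs for the harm row.**
- From the protocol: 1:1 allocation and 250 main-site callers, so about 125 per arm if all respond; 86 staff at each of two centres.
- Assumed, because the article gives no value: 20% harm without streaming; a two-sided 5% test, counted in the harmful direction for callers; independent callers; response from 10% to 100%. Clustering by shift is ignored and would generally lower power further.

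**3. Caller limb.** P(pass) = P(z < 1.96), where z = (p̂₁ − p̂₀) / √(2p̄(1 − p̄)/n). This was computed by exact enumeration of the two binomials.

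| Responders per arm (response) | 20% v 20% | 20% v 30% | 20% v 40% |
|---|---|---|---|
| 125 (100%) | 98% | 55% | 6% |
| 62 (50%) | 98% | 75% | 31% |
| 38 (30%) | 97.5% | 83% | 51% |
| 25 (20%) | 97% | 87% | 65% |
| 12 (10%) | 98% | 93% | 82% |

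Hand check at 125 per arm, 20% v 40%: the SE under the null is √(2 × 0.3 × 0.7/125) = 0.0580, and under the alternative √((0.16 + 0.24)/125) = 0.0566. Then Φ((1.96 × 0.0580 − 0.20)/0.0566) = 6%.

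The first column is flat. The other two rise as responses fall.

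**4. Staff limb.** Two-sample t-test on pre–post change, two-sided 5%; P(pass) = 1 − power.

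| Pairs per site (response) | 0.3 SD difference | 0.5 SD difference |
|---|---|---|
| 86 (100%) | 50% | 10% |
| 43 (50%) | 72% | 37% |
| 26 (30%) | 81% | 58% |

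**5. Both limbs together.** Row GREEN needs both to pass. If only callers are harmed, the row rate is close to the caller figure. If callers go from 20% to 40% and staff differ by 0.5 SD, and the limbs are treated as independent:
- full numbers: 0.06 × 0.10 = 0.6%
- 50% response: 0.31 × 0.37 = 11%
- 30% response: 0.51 × 0.58 = 30%

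**6. An interval rule for callers.** Take a 15-point margin as illustration. With 20% harm in both arms, P(upper 95% limit < 15 points) = Φ(0.15/√(0.32/n) − 1.96): 84% at 125 per arm, 55% at 62, 26% at 25 and 15% at 12. With a true 20-point excess (20% v 40%), Φ((0.15 − 0.20)/√(0.40/n) − 1.96) is about 1% or less at every one of these sizes. Fewer responses now make GREEN harder to reach when there is no harm, and do not open it when there is.

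**The case against.** Several points on the other side stand.

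- **GREEN means proceed to a definitive study.** A reader might infer that the row declares live streaming free of harm. The table does not say so, and harm can be measured again in the larger trial.
- **At the planned numbers a large excess would mostly be caught.** A reader might infer that a large excess would usually pass. For doubled harm the caller limb passes in only 6% of trials at full response and 31% at half. It passes more often than not only at about 30% response or lower.
- **The article does not forecast few responses.** It estimates 250 main-site callers and says only that recruiting them may be difficult. The low response rates above are assumptions.
- **The caution about power is written about exploratory outcome analysis.** It does not name the harm criterion, so the conflict with Table 3 is a tension and not a direct contradiction.
- **Table 3 is the primary basis for the decision, not the only one.** Interviews, observations and free-text answers are also considered, and caller interviewees are chosen partly by whether their survey shows harm.

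None of this repairs the row. The qualitative evidence comes with no rule for overriding a GREEN. Nor can the point be left to the analysis plan: that plan may choose the test, but the three lights are fixed here.

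**Conclusion.** The point holds as a fault in the decision rule. An inconclusive harm comparison counts as GREEN on this criterion, and if there is a true excess the chance of passing grows as responses fall. With no excess it stays near 97.5% at any size.

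How much this matters depends on effect size and response. The rule copes with a doubling of caller harm at full response, but it misses a rise from 20% to 30% in 55% of trials even then. Staff at full numbers pass a 0.3 SD difference in 50%. These are rates for single limbs under the assumptions listed; the row as a whole passes less often if both groups are harmed.

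This should be fixed. It does not reach the highest severity, because GREEN leads to another trial and qualitative data are also weighed.

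**What to change.** Replace the significance wording in the harm row with an interval rule and fill the AMBER cell.

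- **RED:** the lower 95% limit for the excess in harm is above zero.
- **GREEN:** the upper 95% limit is below a margin stated in advance, on the scale of the criterion. For callers this is a difference in rates, for example 15 percentage points; for staff, a difference in mean change.
- **AMBER:** anything else, including too few responses to exclude the margin.

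Apply the rule to callers and staff separately and let the worse light decide. It uses the intervals that the analysis section already promises. It also removes a side effect of the staff wording, under which a significant improvement would fail GREEN without meeting RED.

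The cost is one reworded row and agreement on two margins; the 15 points is an illustration that the team must replace or justify. The downside is that AMBER becomes the likely light when response is low. With 20% harm in both arms, the 95% half-width 1.96 × √(0.32/n) is about 10 points at 125 per arm, 18 at 38 and 22 at 25. At the last two sizes a 15-point margin can be excluded only if the point estimate favours streaming.
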